#### Statistical methods for comparison of baseline study characteristics and safety outcomes

Continuous variables will be summarized with the mean, standard deviation, median and range, and 95% confidence intervals based on the normality assumption. Categorical variables will be summarized using proportions and exact (Clopper-Pearson) 95% confidence intervals will be provided for select summaries. The mITT population is the default population for the efficacy analyses and the Safety population is the default population for safety analyses. For categorical variables, statistical differences between the treatment arms will be assessed by chi-square test or Fisher exact test, as appropriate. For normally distributed continuous variables, Student’s *t*-test will be used to assess the statistically significant differences between the two treatment groups. For non-normal distributed data or where normalization is not possible, nonparametric tests will be used (e.g., Wilcoxon rank sum test), as appropriate. All statistical tests will be two-tailed.

Baseline and co-morbidity factors will be defined as the observations recorded prior to the first study transfusion and will be summarized for the Safety population by treatment received and according to the type of variable (categorical, continuous). Outcome parameters of safety and efficacy will be analyzed for the Safety and mITT populations, respectively, in a similar manner.

Baseline participant demographic and clinical characteristics will be summarized descriptively by study arm and overall. Baseline variables will include age, sex, weight, height, and BMI. The median number of transfusions per participant at the end of the follow-up will also be calculated. Summaries of these variables will be assessed among the mITT, ITT, and PP populations both overall and by treatment arm.

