### Participants

The trial is being conducted by Makerere University-Johns Hopkins University Research Collaboration (MU-JHU) in Kampala, Uganda. The enrolment sites include the Mulago National Referral Hospital (MNRH), Kawempe Specialized National Referral Hospital (KSNRH), and Uganda Cancer Institute Mulago Specialised Women and Neonatal Hospital (UCI). The MNRH, located in Kampala, is the largest public referral and teaching hospital in Uganda with 1500 beds and approximately 3000 patients at any one time and includes the Orthopaedics Department, Surgery Department, and Casualty (i.e., Emergency) Unit. KSNRH is a public 170-bed hospital in Kampala that provides specialist obstetric, gynaecologic, and neonatal care. The UCI is the primary provider of specialized cancer treatment throughout Uganda.

Patients at these locations are eligible for the study if they meet the following inclusion criteria: (1) willing to participate in the study and the patient or legally authorized representative has given written informed consent; (2) transfusion necessary based on a hemoglobin of less than 7 g/dL or clinical judgment of attending physician following the national guidelines; (3) patient agrees to return to the hospital for follow-up visits; and (4) the doctor judges that the patient will be able to complete follow-up visits over the next 10 weeks.

Exclusion criteria (either permanent or temporary) are as follows: (1) presence of red cell alloantibodies; (2) incompatible red cell cross-match (at enrollment prior to first transfusion); (3) expected to require plasma or platelets within the next 10 weeks outside of the WB provided in the trial; (4) blood group Rhesus negative; (5) blood type AB (due to concern of limited supply); (6) weight < 30 kg (due to concern for sufficient blood draws to detect bacteria and other TTIs); (7) HIV-infected; (8) clinical suspicion of sepsis; (9) anti-malarial treatment or indication to be receiving malaria prophylaxis (e.g., sickle cell disease or ongoing pregnancy) within 7 days prior to randomization; (10) fever (central body temperature greater than 38.5 °C); (11) transfusion(s) of a blood product within 1 month prior to randomization; (12) acute or chronic medical disorder that, in the opinion of the investigator, would impair the ability of the patient to receive protocol treatment; and (13) previously enrolled and randomized in this trial or any other pathogen reduction trial.

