*Pre-transfusion*: enrollment of the recipient and blood collected to evaluate baseline infectious status and RBC compatibility and antibody identification. RBC compatibility and antibody identification consist of verifying the ABO group of the unit, ABO/Rh testing and 37oC Coombs antibody screen for the recipient, and a serological cross-match at room temperature; in the event that a participant develops a clinically significant RBC alloantibody during the study and requires further transfusion, appropriate 37°C pre-transfusion testing/cross-match will be performed.*At 2–6 h following transfusion*: assess hemoglobin increment with CBC and clinical evaluation for possible acute transfusion reactions, as defined by the US CDC Hemovigilance criteria [31].*Within 48 h (+ 1 day)* of each transfusion: blood collected for bacterial culture and malaria identification.*At 7 days (− 1 to + 2 days)* after the transfusion: obtain brief medical history focused on signs or symptoms of transfusion reactions and infections with HIV, HBV, HCV, HEV, HHV-8, or malaria. Blood collected for TTI testing and evaluation for transfusion reaction.*At 4 weeks (−4 to + 7 days)* after the transfusion: obtain brief medical history focused on signs or symptoms of infection with HIV, HBV, HCV, HEV, HHV-8, or malaria. Blood collected for TTI testing.*At 10 weeks (−7 to + 14 days)* after the first transfusion: obtain brief medical history focused on signs or symptoms of transfusion reactions and infections with HIV, HBV, HCV, HEV, HHV-8, or bacteria. Blood collected for TTI testing and evaluated for delayed transfusion reaction/new antibodies with antibody screen.

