### Intervention outcomes

The primary endpoint of this study is the incidence of any pre-defined viral, bacterial, or parasitic TTI: HIV, HBV, HCV, HEV, HHV-8, bacteria, or malaria in a previously negative recipient for the specific TTI as indicated by changes in laboratory findings at day 2, day 7, week 4, or week 10 after the first transfusion. A TTI will only be ascribed when both the donor unit and recipient have the exact same pathogen as confirmed by specialized laboratory testing.

In addition, the clinical effectiveness of Mirasol-treated WB products compared to standard WB products in recipients will be evaluated by the following:
Incidence and characteristics of acute transfusion reactions as defined by CDC Hemovigilance [31]Change in hemoglobin level post-transfusion compared to pre-transfusionDelayed transfusion reactions/neoantigenicity
i)Incidence of an amnestic RBC alloantibody as detected by a positive direct antiglobulin test (DAT) when participants are evaluated for transfusion reactionii)Incidence of new red cell alloantibodies post-transfusion (positive antibody screen at 10 weeks)Incidence of treatment-emergent adverse events (TEAE) and treatment-related adverse events

In order to assess the primary and secondary outcomes, the following laboratory tests will be performed (Fig. 1):

● Complete blood counts (CBCs)

● RBC antibody screen and direct antiglobulin test (DAT). The antibody screen will be used to determine new RBC alloantibody identification. If there is a suspected acute hemolytic transfusion reaction, a DAT will be performed. If the DAT is positive, antibody identification will be performed to determine whether it is a RBC alloantibody or a new antibody due to Mirasol PRT [32, 33].

● Bacteria: Cultures will be performed for both the donor unit and recipients. A TTI will only be ascribed when both the donor unit and recipient have the exact same genus and species.

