#### Stopping rules

An interim analysis for efficacy with respect to the primary outcome (incidence of any study TTI) will be performed when 10-week outcome data are available for the first 1000 randomized transfusions. The Lan-DeMets implementation of the O’Brien-Fleming procedure will be used for this single interim analysis; the alpha level will be set to 0.00304, with the final testing alpha set at 0.04895 to maintain the overall alpha of 0.05 [45]. Under the protocol-specified efficacy of 80%, there is 49% power for this interim criterion to be met. If this criterion at 1000 is met, and at least 25% of the observed reduction is due to reduction in pathogens other than malaria, then stopping for efficacy may be recommended. A futility analysis will also be performed in the event the stopping rule is not met. Under the assumption that the future events are affected by the protocol-specified 80% reduction parameter, the conditional probability of the final *p*-value being less than 0.04895 will be calculated; if it is less than 10%, early termination may be recommended due to futility.

The Safety population will consist of all randomized subjects who undergo at least one study transfusion, independent of the outcome or successful completion of the procedure. Summaries by treatment group will be based on the treatment actually received. Specifically, the safety analyses will evaluate adverse transfusion reactions, delayed transfusion reactions, hemoglobin increments, treatment-related adverse events, and all-cause mortality. The trial might also be stopped if there are safety concerns.

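### Haemoglobin change is to be compared without adjusting for the pre-transfusion value; a baseline-adjusted model costs nothing and, in large samples, is never less precise

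*Protocol article*

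**What the plan says.** The section on statistical methods for baseline characteristics and safety outcomes sets a default. For normally distributed continuous variables, Student's t-test "will be used to assess the statistically significant differences between the two treatment groups". Otherwise, "For non-normal distributed data or where normalization is not possible, nonparametric tests will be used". It then carries these methods over to the outcomes: "Outcome parameters of safety and efficacy will be analyzed for the Safety and mITT populations, respectively, in a similar manner". No covariate is named.

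Haemoglobin falls under this rule by two routes. Under Intervention outcomes, "the clinical effectiveness of Mirasol-treated WB products compared to standard WB products in recipients will be evaluated by the following", and change in haemoglobin is the second of four items, with no ranking among them. Under Stopping rules, "Specifically, the safety analyses will evaluate adverse transfusion reactions, delayed transfusion reactions, hemoglobin increments", and for that population "Summaries by treatment group will be based on the treatment actually received". The visit schedule under Assignment of intervention places the measurement 2–6 h after transfusion, to "assess hemoglobin increment with CBC and clinical evaluation for possible acute transfusion reactions".

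**The concern.** Taking a change score is not the same as adjusting for baseline. The change score fixes the coefficient of the pre-transfusion value at 1, whereas ANCOVA estimates it. Where the true coefficient differs from 1, the unadjusted comparison has a larger variance than it needs. Part of any chance difference between the arms in starting haemoglobin also stays in the estimated treatment difference.

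What is at stake is the width of the interval for one secondary measure: how closely the haemoglobin response to treated blood can be compared with the response to standard blood. The type I error of the planned test and the primary conclusion on transfusion-transmitted infection are not at stake.

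**Working it through.** **Inputs from the article.** 1000 per arm, 1:1; 850 per arm after the assumed 15% loss by 10 weeks, which should matter little for a measurement at 2–6 h. The outcome is change from before to after transfusion. The article gives no haemoglobin SD, correlation, target difference, margin or power, so there is no stated haemoglobin figure to reproduce. Its 97% power concerns the infection endpoint only.

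**Inputs assumed.** Pre- and post-transfusion SDs s0 and s1 of 1.5 to 2.0 g/dL, correlation ρ of 0.3 to 0.9, and an illustrative difference of 0.3 g/dL.

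**Formulas (variance per participant).**
- Change score: s0² + s1² − 2ρ·s0·s1
- ANCOVA: s1²(1 − ρ²)
- Change score minus ANCOVA: (s0 − ρ·s1)², which is never negative. It is zero only when the slope of post on pre, ρ·s1/s0, equals 1.
- Equal SDs: ratio of ANCOVA to change score = (1 − ρ²)/[2(1 − ρ)] = (1 + ρ)/2
- 95% CI half-width: 1.96 × √(2/n × variance)

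**Equal SDs of 1.5 g/dL, n = 1000 per arm.**

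| ρ | Variance ratio | Half-width, change score (g/dL) | Half-width, ANCOVA (g/dL) |
|---|---|---|---|
| 0.3 | 0.65 | 0.156 | 0.125 |
| 0.5 | 0.75 | 0.131 | 0.114 |
| 0.7 | 0.85 | 0.102 | 0.094 |
| 0.8 | 0.90 | 0.083 | 0.079 |
| 0.9 | 0.95 | 0.059 | 0.057 |

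For ρ = 0.5 in full: the change-score variance is 2 × 2.25 × 0.5 = 2.25, and 1.96 × √(2/1000 × 2.25) = 0.131. The ANCOVA variance is 2.25 × 0.75 = 1.6875, and 1.96 × √(2/1000 × 1.6875) = 0.114.

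**Unequal SDs, ρ = 0.5 to 0.9.**
- s0 = 2.0, s1 = 1.5: ratio 0.50 to 0.56.
- s0 = 1.5, s1 = 2.0: ratio 0.89 to 0.995. At ρ = 0.7 it is 4 × 0.51 / (2.25 + 4 − 4.2) = 2.04/2.05 = 0.995, so almost nothing is gained.

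**Power for a difference of 0.3 g/dL.** With SD 1.5, ρ = 0.5 and 1000 per arm, power goes from 99.4% to 99.9%. In a less favourable case (SD 2.0, ρ = 0.3, 850 per arm) it goes from 74% to 90%.

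**Residual imbalance.** With SD 1.5 and 1000 per arm, the standard error of the baseline difference between arms is 1.5 × √(2/1000) = 0.067 g/dL. At slope 0.5 the change score leaves 0.5 × 0.067, or about 0.03 g/dL, with sign opposite to the imbalance.

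**The case against.** The strongest case against is that this is a default sentence covering every continuous variable. It never names haemoglobin, and the full statistical analysis plan may already specify an adjusted model. The planned test is valid under randomisation, and at this sample size the interval is narrow either way. All of that stands except the first step. The article does assign a method to outcomes as well as to baseline variables, and haemoglobin change is among those outcomes, so the unadjusted comparison is a stated choice.

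A reader might also infer several stronger points that the article does not support:

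- **That haemoglobin is the main effectiveness outcome.** It is one of four unranked measures, is also filed under safety, and has no power calculation or comparability margin.
- **That baseline haemoglobin is recorded for everyone.** The text does not say so. Eligibility is "transfusion necessary based on a hemoglobin of less than 7 g/dL or clinical judgment of attending physician following the national guidelines", so a value below the threshold is not always the basis for entry. The pre-transfusion value is implied by the definition of the outcome. That is enough here, because the t-test on change and the ANCOVA need the same measurement.
- **That baseline imbalance passes straight into the result.** Baseline is already subtracted, so only the fraction (1 − slope) remains.
- **That the t-test breaks independence because about half of participants are expected to have two or more transfusions.** Nowhere does the article say that increments are pooled per transfusion, and it defines baseline as before the first study transfusion, which fits one value per participant.

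**Conclusion.** The point holds as a free improvement, not as an error. As written, the rule compares haemoglobin change without adjustment, and ANCOVA on the pre-transfusion value is never less precise in large samples. The size of the gain cannot be fixed from the article. Under assumed equal SDs the variance falls by 35% (ρ = 0.3) down to 5% (ρ = 0.9). With unequal SDs the saving ranged from about half to almost nothing in the cases tried. In absolute terms it is usually small: about 0.02 g/dL or less off the half-width at SD 1.5, ρ of 0.5 to 0.8 and 1000 per arm. It becomes material only with a larger SD and a weak correlation. The primary infection analysis is unaffected.

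**What to change.** State, before unblinding, that the main haemoglobin comparison is an ANCOVA of haemoglobin after the first study transfusion on arm and pre-transfusion haemoglobin, reported as an adjusted difference with its 95% CI. Weight may be added. It is already a listed baseline variable, and the response to a unit of near-standard volume can be expected to vary with body size. Keep the t-test or rank test on the change as a supporting analysis. If increments from repeat transfusions are also analysed, use a model that allows for clustering within participant, such as a mixed model with a participant random effect.

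The cost is a few sentences of analysis wording. No extra participants, visits or assays are needed, because the change outcome already requires both haemoglobin values.

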### Trial organization, monitoring, and safety

Quality and accuracy of the data are monitored and assured by FHI Clinical, an independent commercial Clinical Research Organization with extensive experience designing and managing clinical research in resource-constrained settings. Monitoring is conducted after every 100 new participants are enrolled.

The DSMB is comprised of individuals with expertise in transfusion medicine, infectious diseases, statistics, and clinical trial design and conduct. The DSMB sits regularly and reviews reports of trial data.

The severity of adverse experiences is graded using the NIH DAIDS Toxicity Guidelines version 2.0 [46]. All SAEs are reported in narrative form to the IRBs within 2 weeks of the site’s awareness of the event. Deaths are reported within 3 days of the site’s awareness, which is in line with the Uganda National Council of Science and Technology (UNCST) guidelines.

The study team will ensure the proper care and management of any adverse events related to the intervention arm.

### Dissemination

Participants will be informed about any positive results that could improve their own health, specifically treatable TTIs.

The research findings will be communicated through meetings with the study participants, conference presentations, and peer-reviewed publications to the scientific community and through reports and workshops to the funder and Ugandan Ministry of Health. Authorship will be determined via the International Committee of Medical Journal Editors (ICMJE) recommendations. Participant-level data will also be available from the corresponding authors.

## Discussion

Established TTIs, emerging, re-emerging, and novel pathogens all pose risk to global blood transfusion safety. This concern is heightened with the continued emergence of new pathogens worldwide. The pursuit of transfusion safety through targeted pathogen testing continues to add incremental cost to blood components without addressing the urgent need of emerging infections [47]. Additionally, even when screening tests are added for selected pathogens, patients remain at risk during the time taken for assessment, test development, and policy implementation. As one example, it took over a decade from recognition of risk to adoption of screening for *Babesia* in the USA [48, 49]. Pathogen reduction may be able to reduce some of these screening assays (e.g., syphilis) while responding to intense needs for blood supply.

Numerous factors have been cited for the accelerating threat of emerging infectious diseases (EID). These include the increase in access, ease, and speed of international travel; the effect of immigration on disease introduction in new regions; the inadvertent importation of disease vectors; the re-emergence of previously controlled infections; the increase in ranges for disease vectors due to climate change; the increased overlap between human and wild habitat; and the migration of animal hosts such as birds and deer [47, 50, 51]. Any infection with an asymptomatic blood-borne phase has the potential for transfusion transmission [50, 52]. Historically, the response to an EID has involved monitoring for disease emergence, identification of the disease-causing agent, analysis of epidemiological risk factors, definition of donor deferral criteria, and, if justified, development of a specific screening assay [50]. The current system for assuring the safety of the blood supply relies upon donor deferral procedures, EMA/FDA-licensed serological and/or nucleic acid testing assays that target specific transfusion-transmitted pathogens, and blood filtration procedures/leukoreduction. Not only is this inefficient, costly, and slow given the need for de novo test development or adaptation (replete with regulatory hurdles), it fails to address the complete spectrum of pathogens known, emerging, or re-emerging that threaten the blood supply. In contrast to the reactive strategy (deferral of donors, testing of donated blood) for blood safety, PRT offers a generalized, proactive mechanism to reduce or eliminate the threat of malaria and EID transmission by transfusion [47, 50]. The additional benefits of reducing alloimmunization, transfusion-associated graft versus host disease (TA-GvHD), and non-infectious transfusion reactions are also of high value.

Currently, no FDA-approved PRT system is available for use with WB or red blood cells, the two most commonly transfused blood products worldwide; the Mirasol PRT system is uniquely positioned to fill this gap. WB is used commonly in low-to-middle-income countries and in military trauma, but rarely in high-income countries; however, there is an increasing interest in its use for resuscitation in civilian trauma accompanied by massive hemorrhage because of comparable survival with when blood components are used and the logistical and economic advantages [43, 53–55]. Mirasol PRT has been shown to be effective across different classes of pathogens including bacteria, viruses, and parasites in vitro and for plasma and platelets [56]. If shown to be effective for WB, it could represent a fast, cost-effective way of making WB transfusions safe from both known and unknown pathogens.

There are potential limitations and challenges with MERIT. One potential limitation of this clinical trial may occur if the rate of TTIs in our study is lower than expected. However, we used conservative estimates for all of the TTIs. The study is also powered off the combined outcome of multiple TTIs, and the study power, at 97%, is robust to lower-than-expected incidence for any of these TTIs. In addition, there are risks of poor follow-up or participant loss due to mortality since many of the Ugandan patients requiring blood transfusion are very sick. However, MU-JHU closely engages study subjects and consistently has a < 10% loss with clinical trials requiring a 1–2-year follow-up. In addition, monitoring the blood inventory for both standard WB and Mirasol-treated WB is a challenge as the Mirasol-treated units only have a shelf life of 21 days (the same was adopted for the standard units to maintain blinding). Finally, the COVID-19 pandemic has affected all research globally and has not spared the MERIT trial; not only has it meant that the study staff are at risk of contracting the SARS-CoV2 virus while executing their duties, but the lock-downs and travel restrictions have meant scale down of activities at the recruitment sites and difficulties following participants that have to be overcome.

The MERIT trial will assess the efficacy of Mirasol PRT to reduce or eliminate TTIs from WB particularly in a resource-limited environment. If the trial demonstrates efficacy, PRT technology may represent a cost-effective, easy-to-use, and feasible technology whose implementation might improve the health of people especially in resource-limited settings or where a full blood screening program is not available.

